## Introduction

People with visual impairment (VI) face a higher risk of psychological distress, which affects their multidimensional health aspects [1]. The mortality rate among the visually impaired is much higher than that of normally sighted people [2]. Visual impairment, characterized by low vision or blindness, is a functional limitation of the eyes. At least 2.2 billion people worldwide are visually impaired, and this is gaining growing concern in the development of public health policies [3]. Based on global population growth and increased life expectancy, it is estimated that global blindness will triple and moderate-to-severe VI will double by the year 2050 [4]. Though VI affects hundreds of millions globally, 90% of those with VI live in low- and middle-income countries [5]. India contributes 8 million people with blindness and 62 million with VI to the global population [6]. 

Loss of vision affects various aspects of life, such as reduced physical activities, unintentional injuries, loneliness, disturbed sleep, and low self-esteem [7-12]. Compared with the general population, people with VI are at a higher risk of experiencing psychological distress, such as anxiety and depression [13,14]. In return, the accumulated stress can lead to more vision loss [15]. Various factors contribute to psychological distress in the visually impaired, such as poor social communication, compromised daily role functions, and self-care capacities [16-19]. In addition, they face a higher chance of unemployment and more stress from family responsibilities and marriage expectations than their sighted peers [20-22]. Psychological distress in VI induces fatigue, low self-esteem, caregiver distress, and socioeconomic burden at large [23-26]. In addition, people with VI, especially those with no perception of light, tend to experience poorer sleep quality than the sighted due to the desynchronized rhythm of melatonin secretion [11]. Sleep disturbance is a mediating factor in mental health, and sleep management has been used as an effective strategy to treat mental disorders [27].

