The primary outcome will be the level of psychological distress assessed using the Hospital Anxiety and Depression Scale (HADS). Additionally, psychological well-being will be evaluated using the Oxford Happiness Questionnaire (OHQ), while psycho-hormonal well-being will be examined through the analysis of biomarkers such as dopamine, serotonin, cortisol, endorphin, and melatonin. The secondary outcomes will encompass psychophysiological well-being assessed by heart rate variability (HRV), electrocardiograph (ECG), galvanic skin resistance (GSR), respiratory rate (RR), and electromyography (EMG). Functional balance, mobility, and fall risk will be evaluated using the Time Up and Go test (TUG). Strength and endurance will be measured using the 30-second Chair Stand Test (30 CST). Social well-being will be assessed using the Multidimensional Scale of Perceived Social Support (MSPSS), while the Spiritual Well-being Scale (HWS), health-related quality of life will be measured by the Vision Quality and Life Index (VisQoL), and sleep quality will be assessed using the Pittsburgh Sleep Quality Index (PSQI).

Primary Outcomes

Psychological well-being in terms of anxiety and depression will be measured by the Hospital Anxiety and Depression Scale; happiness will be measured by the Oxford Happiness Questionnaire; and its related hormonal changes will be measured by dopamine, serotonin, endorphin, cortisol, and melatonin.

Hospital Anxiety and Depression Scale (HADS): Psychological well-being in terms of anxiety and depression will be measured by the HADS. This scale has been suggested for the population with VI [57]. The HADS consists of two subscales: anxiety and depression. Each subscale consists of seven items, each rated on a four-point Likert scale ranging from 0 to 3. A score of eight or above on each subscale and 15 or above on the full scale represents a clinically relevant cut-off value to detect anxiety and depressive symptoms. The English version of HADS has demonstrated satisfactory validity and reliability, with a Cronbach's alpha of 0.80 for the depression subscale and 0.81 for the anxiety subscale. The correlations between the two subscales, anxiety (HADS-A) and depression (HADS-D), varied from 0.40 to 0.74 (mean of 0.56). An optimal balance between sensitivity and specificity was achieved when the score reached eight or above on both HADS-A and HADS-D [58,59]. 

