Oxford Happiness Questionnaire (OHQ): The Oxford Happiness Questionnaire will measure psychological well-being in terms of happiness. This scale has been used in the population with VI compared with the normal-sighted participants of the same age [60]. The OHQ consists of 29 items, rated by a six-point scale each (range: 1-6). It has demonstrated excellent validity and reliability with a Cronbach's alpha of 0.92 [61]. A lower score indicates a lower level of happiness. 

Biomarkers: Subjective psychological questionnaires are self-evaluated reports; objective biochemical tests have been suggested as supportive evidence from previous research to elucidate the mediating effects of MY and PE on stress and mood changes in the progression of depression and anxiety in individuals with VI [39]. Biochemical tests of dopamine, serotonin, cortisol, and endorphin are used as biomarkers to correlate with mood changes. In addition, melatonin, a neurotransmitter that regulates sleep and wakes rhythm and is closely related to psychophysiological well-being, will be assessed. Eight milliliters of blood samples will be withdrawn and centrifuged. Serum and plasma will be separated and stored at a -80-degree centigrade freezer in multiple aliquots until further processing. Higher values of dopamine, endorphin, serotonin, and melatonin indicate subjective well-being [62-64], whereas lower levels of cortisol reveal a less stressful state of mood [65]. These biomarkers indicate hormonal balance or homeostasis, which in turn affect mental and physical health [66].

Secondary Outcomes

Since psychological well-being is closely related to physiological, physical, social, and spiritual well-being, as well as health-related quality of life and sleep quality. Hence, these factors will be included as secondary outcomes.

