Spiritual Well-being - Holistic Well-being Scale (HWS): The 30-item Holistic Well-being Scale (HWS) is a scale of spiritual well-being containing good psychometric properties and validity. It evaluates two core concepts of holistic well-being, which are: 1) the absence of affliction characterized by emotional vulnerability, bodily irritability, and spiritual disorientation; and 2) the presence of equanimity regarding non-attachment, mindful awareness, general vitality, and spiritual self-care. Holistic well-being focuses on the interconnectedness of body, mind, and spirit as well as spirituality, which is different from religiosity but fundamental values, beliefs, and meanings of life. Each item is a 0-10 scale ranging from "totally disagree" to "totally agree." Higher scores represent a deteriorated state of holistic well-being. [79,80].

Health-related Quality of Life - Vision Quality of Life Index (VisQoL): The Vision Quality of Life Index (VisQoL) is a short-form, six-item questionnaire used to quantify the impact of VI on the quality of life of visually impaired individuals [81]. This questionnaire assesses the following six domains: physical well-being, social well-being, emotional well-being, level of independence, self-actualization, planning, and organization. The reliability value of the Indian language version (Hindi & Telugu) exceeds 0.80. It satisfies the Rasch measurement model requirement with excellent psychometric properties as a simple summative instrument [82]. Higher scores indicate worsened QoL.

Sleep Quality - Pittsburgh Sleep Quality Index (PSQI): Pittsburgh Sleep Quality Index (PSQI) is a time-efficient self-reported sleep quality inventory to assess sleep quality and disturbance over the last month. The 19 items in the Likert-type response evaluate sleep latency, duration, and sleep disturbance [83]. It shows high test-retest reliability with Cronbach’s alpha of 0.87 and has demonstrated good validity with high correlations between PSQI and sleep log data. Sleep is considered disturbed if the value is above 5, with a sensitivity of 98.7 and a specificity of 84.4 [84]. Previous research has reported longer sleep latency and disturbed sleep cycles in individuals with VI [85].

Data collection

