Prior to commencing any data collection, the data assessors will undergo training regarding the principle of data collection. The data collection procedure will be closely monitored to ensure data quality. In case of any confusion, the data assessors are directed to consult the principal investigator to clear the doubt. If any misinterpretation or misleading of the participants during the subjective psychological questionnaire interview, the data will not be considered.

Data collection at every time (T0, T1, and T2) will need approximately two weeks. Blood collection will be conducted first, followed by ECG recording, questionnaire interview, and physical test. Participants will not be occupied for more than 30 minutes daily for data collection so that their daily study routine will not be interrupted. Laboratory technicians will collect blood in the early morning from 6-9 am with fasting blood. Food and beverage will be provided once the blood collection completes for everyone as breakfast. Each day blood collection will cover around 15-20 participants so that participants do not have to wait too long with an empty stomach. The procedure will be done at the participant’s convenience to complete the follow-up. Data collection for the subjective questionnaire will be in the form of a one-to-one oral assessment, i.e., one participant and one data collector, to protect the participant's privacy.

Data collectors will confirm the time availability of the participants before the visit. The research team will get permission from the authorities before the visit for each data collection. Participants who discontinued the study intervention will be excluded. The principal researcher will keep a record of the reasons for dropping out. Once data is collected, the study investigator will enter the data with the participants’ names coded. The raw data will be stored in a locker, and only the principal investigator can access it. The research assistant will double-check the data entry in case of any mistakes.

Attrition and missing data 

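### The direction-of-benefit rule for the Holistic Well-being Scale contradicts its own equanimity domain, and a 6-9 am melatonin level cannot carry the stated higher-is-better reading

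*Protocol article*

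**What the plan says.** **HWS.** Under Secondary Outcomes, the article describes a 30-item scale with two core concepts. One is the absence of affliction (emotional vulnerability, bodily irritability, spiritual disorientation). The other is "the presence of equanimity regarding non-attachment, mindful awareness, general vitality, and spiritual self-care". Every item is scored 0 to 10 by strength of agreement. One rule then covers the whole scale: "Higher scores represent a deteriorated state of holistic well-being". The article states no reverse coding and no scoring by domain.

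**Melatonin.** The Primary Outcomes subsection lists it among the hormonal measures: "its related hormonal changes will be measured by dopamine, serotonin, endorphin, cortisol, and melatonin". The Biomarkers paragraph gives the reading rule, "Higher values of dopamine, endorphin, serotonin, and melatonin indicate subjective well-being", and calls melatonin "a neurotransmitter that regulates sleep and wakes rhythm and is closely related to psychophysiological well-being". The Introduction says that people with visual impairment, especially those without light perception, "tend to experience poorer sleep quality than the sighted due to the desynchronized rhythm of melatonin secretion". The Data collection section fixes the sampling time: "Laboratory technicians will collect blood in the early morning from 6-9 am with fasting blood". No other sampling time is described.

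**The concern.** A direction rule decides whether a difference between arms is reported as benefit or harm. The HWS rule suits affliction but not equanimity. Equanimity includes mindful awareness, which the Strengths section names as what the comparison of yoga with physical exercise should bring out. The second hypothesis also claims superiority of yoga on spiritual well-being. The misreading would therefore fall on the construct meant to separate the arms. If the items were summed without reversal, real improvement in the two domains would also pull the total in opposite directions.

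For melatonin, the article locates the problem in the timing of secretion but plans to read the amount found in a morning sample. In a person whose rhythm is displaced, that amount depends on where in the cycle the morning falls. A rise or a fall then has no fixed meaning for well-being.

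**Working it through.** There is no stated figure to reproduce; the point concerns how results are read. Two illustrative checks show how large the problem could be.

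**1. HWS**

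Inputs: 30 items, each 0-10 by agreement, one rule of higher = worse (all from the HWS paragraph). Assumptions: k of the 30 items belong to equanimity, with k between 10 and 20 because the article gives no split; every item improves by 1 point.

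- Equanimity items rise: +k.
- Affliction items fall: -(30 - k).
- Unreversed total: k - (30 - k) = 2k - 30.
- Total with equanimity reversed: -k - (30 - k) = -30.

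| k | Unreversed change | Change with equanimity reversed |
|---|---|---|
| 10 | -10 | -30 |
| 12 | -6 | -30 |
| 15 | 0 | -30 |
| 18 | +6 | -30 |
| 20 | +10 | -30 |

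Below 15 equanimity items the improvement is understated, at 15 it vanishes, and above 15 it reads as harm. A separate equanimity score read by the stated rule is mislabelled whatever k is.

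**2. Melatonin**

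Input from the article: sampling between 06:00 and 09:00. Assumptions, none of them from the article: secretion follows a bell-shaped daily pulse of fixed height with SD s of 2 to 3 h, an aligned rhythm peaks at p = 02:00 to 04:00, and draws are spread evenly over the window. The level at time t is exp[-(t - p)²/(2s²)], with time differences taken around the 24 h clock.

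Mean 6-9 am level relative to an aligned rhythm, over the assumed range:

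| Displacement | Ratio |
|---|---|
| 3 h delay | 1.9 to 12.7 |
| 6 h delay | 1.4 to 23.6 |
| 12 h shift | 0.00 to 0.54 |

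Across all possible phases, 29% to 46% give a higher morning level than the aligned rhythm and the rest do not. The height of the pulse is the same throughout, so the differences come from phase alone. Better alignment could lower or raise the morning value.

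Draw time matters too. For an aligned rhythm the 06:00 to 09:00 ratio is exp[((9 - p)² - (6 - p)²)/(2s²)] = exp[(45 - 6p)/(2s²)].

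- p = 4, s = 3: exp(21/18) = 3.2.
- p = 2, s = 2: exp(33/8) = 61.9.

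**The case against.** **HWS.** The rule is right for affliction, and right for a total in which equanimity is reversed. Scoring detail often sits in the scale's source, the full protocol or the analysis plan, and a condensed article may leave it out. This stands against any claim that the analysis itself is shown to be wrong. It does not rescue the sentence as printed, because the article does not merely omit the direction: it states one that clashes with its own description of the scale. A reader might also infer that the total cancels exactly. That needs an unreversed sum and 15 equanimity items out of 30, and the article gives neither. It is also true that flipping the sign of a single score leaves the planned ANOVA F test unchanged. An unreversed sum is different, because it shrinks the signal being tested.

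**Melatonin.** A reader might infer that the rule is backwards. The documents do not show that: the article cites sources for it that cannot be checked here, and the Introduction describes a tendency, strongest without light perception. The share of such participants is not given.

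A reader might also infer that a drifting rhythm puts baseline and eight-week samples at unrelated phases. That rests on an assumed drift. At 10 to 30 minutes a day, 56 days gives 560 to 1,680 minutes, or 9.3 to 28 h. About 25.7 minutes a day (1,440/56) returns a participant to the same phase, and 28 h is a net shift of only 4 h. The interval is not exactly 56 days either, since each assessment round takes about two weeks.

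Nor is bias between arms shown. Randomisation is stratified by severity and the same morning window applies at each visit, so scatter in phase would mainly add noise. That answers a charge of bias, but it does not tell the reader what a rise or fall means.

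Finally, the Outcomes section names HADS as the primary outcome and the Biomarkers paragraph treats the assays as supportive. That limits the consequence, although melatonin is still listed under Primary Outcomes.

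**Conclusion.** The point holds in two parts of unequal strength.

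**HWS** is the firmer part. The contradiction lies within one paragraph and needs no outside assumption. Followed literally, the rule mislabels a gain in equanimity as deterioration. How far an unreversed total would be diluted depends on the item split: under the assumed 10 to 20 equanimity items, a uniform one-point improvement gives -10 to +10 instead of -30. The HWS is a secondary outcome.

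**Melatonin** is an unsupported reading. Given the rhythm problem that the article describes, a 6-9 am level cannot be called better because it is higher. The direction is indeterminate. The ratios above rest on assumed pulse shapes; they show that phase can dominate the value, not what will happen in this sample.

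Both should be corrected before analysis. Neither affects HADS.

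**What to change.** **HWS.** Replace the single direction sentence. Analyse affliction (higher = worse) and equanimity (higher = better) as two scores, and use a total only with equanimity reverse-coded. This costs one sentence and no new data.

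**Melatonin.** Remove it from the higher-is-better rule, describe it as a 6-9 am level, and treat it as exploratory or supportive. Report it by the severity strata already used for randomisation; light perception is not among the variables the article lists. Record the clock time of each remaining draw.

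The cost is that melatonin loses its listing under Primary Outcomes. The Trial status section says that 62 participants were already recruited in two centres, that intervention began in August 2022 and that data collection continues. Draw times for earlier samples may therefore not be recoverable. Wake-time recording and matched draw slots cannot be imposed on samples already taken, and adjusting cortisol for time since waking goes beyond the defect shown here. Date and document both changes before results by arm are examined.

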**Figure 1 FIG1:**
[figure not shown]
Consolidated Standards of Reporting Trials (CONSORT) flow diagram of the study T0 - baseline; T1 - at the perception of intervention (eight weeks); T2 - six months following the intervention

**Table 1 TAB1:** Standard Protocol Items: Recommendations for Interventional Trials (SPIRIT) HADS,- Hospital Anxiety and Depression Scale; OHQ - Oxford Happiness Questionnaire; ECG - electrocardiograph; HRV - heart rate variability; RR - respiratory rate; GSR - galvanic skin resistance; EMG - electromyography; TUG - Time Up and Go Test; 30CST - 30-second Chair Stand Test; MSPSS - Multidimensional Scale of Perceived Social Support; HWS - Holistic Well-being Scale; VisQoL - Vision Quality of Life Index; PSQI - Pittsburgh Sleep Quality Index; T0 - baseline; T1 - at the completion of intervention (eight weeks); T2 - six months following the intervention

	Enrolment	Allocation	Post-allocation			
Timepoint	0	0	T0	Intervention	T1	T2
Enrolment						
Eligibility screen	X					
Ophthalmology test		X				
Oral Informed consent with fingerprint	X					
Allocation		X				
Interventions						
Mindfulness-based yoga				X		
Physical exercise				X		
Wait-list control				X		
Assessment						
Sociodemographic characteristics			X			
HADS, OHQ, biomarkers, ECG, HRV, RR, GSR, EMG, TUG, 30 CST, MSPSS, HWS, VisQoL, PSQI			X		X	X
Treatment-related Information: adverse events, adherence to assigned treatment			X		X	X
Potential confounders: food			X		X	X

Objectives and hypothesis

The objectives will be as follows: to investigate the effect of mindfulness-based yoga (MY) on 1) psychological well-being, 2) physical well-being, 3) physiological well-being, 4) spiritual well-being, 5) health-related quality of life, and 6) sleep quality in individuals with early moderate-to-severe visual impairment and blindness.

We hypothesize that 1) the MY program will effectively improve psychological well-being, physiological well-being, physical well-being, social well-being, spiritual well-being, vision-related quality of life, and sleep quality in individuals with early VI, and 2) the MY will be superior to PE in improving psychological well-being, physiological well-being, physical well-being, social well-being, spiritual well-being, vision-related quality of life, and sleep quality in individuals with early VI.

Design

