Inclusion and exclusion criteria

Inclusion criteria include the following: 1) a clinical diagnosis of early VI, with a visual disability severity rating of moderate-to-severe VI according to WHO International Disease Classification 11 Distance Visual Impairment [48]; 2) age between 15-25 years old; 3) early visual impairment, early VI refers to people who have been blind since birth or early childhood (<5 years), whereas late VI indicates persons who lost sight after learning to read print [49]; (4) participants who are willing to give oral consent or assent along with a thumbprint. For participants under 18 years old, a consent form signed by their legal guardian will be needed as well.

Exclusion criteria are the following: 1) participants who are receiving treatment for mental disorders currently or with uncontrolled mood disorders; 2) current participation in any other pharmacological trial or cognitive behavioral program; 3) cognitive impairment such as mental retardation; 4) other debilitating medical conditions except VI, such as having a hearing impairment, epilepsy, or physical disability (e.g., deformity of limbs), that can impede full participation in the study; 5) having a secondary VI, such as Grave's ophthalmopathy (thyroid eye disease), Bechet syndrome (blood vessel inflammation throughout the body), uveitis (inflammation of the middle layer of the eye), multiple sclerosis (autoimmunity), in which symptoms are caused by a different system disorder or another illness [23].

The inclusion criteria are to maximize the enrolment of appropriate participants, while the exclusion criteria are used to screen out participants who are with medical conditions for which yoga or exercise is contraindicated, which pose a safety risk, preclude fully informed consent, or hinder compliance with interventions (e.g., mental retardation).

Sample size

A previous study on children (9-16 years) with VI reported a moderate effect size of 0.4 for overall well-being [37]. To anticipate a similar effect size of at least 0.4 on adolescents and young adults (15-25 years) and using the software G Power 3.1 with 80% power at a 5% level of significance, 36 subjects will be in each arm of the study. Considering an attrition rate of 20%, we will recruit 132 subjects, with 44 per arm.

Interventions

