Physiological well-being: Physiological measurement will adopt an instrument called physiography (RMS Polyrite-D) with four channels measuring heart rate variability (HRV), electrocardiography (ECG), galvanic skin resistance (GSR), respiratory rate (RR), and electromyography (EMG). Researchers will use medically graded disposable electrodes positioned on both arms and right leg to record ECG and HRV. Respiratory data will be acquired using a respiratory belt with a sensor attached. Two sensors placed on the index and middle fingers will acquire the data for GSR. The recording of EMG will be conducted with two electrodes placed on both cheeks. These variables are closely associated with autonomic tone. A higher HRV indicates less stress and a relaxed mood, while a lower value depicts stressful conditions due to a higher sympathetic tone [67]. A higher value of RR reveals stressful states such as anger and anxiety, while a lower rate of respiration indicates relaxation and well-being [68,69]. As a person becomes more stressed, GSR increases [70]. Higher EMG suggests a higher stress level [71]. Previous research has demonstrated that children with VI had significantly higher rates of breathing and heart rates than normal-sighted children of the same age [72].

Physical well-being - Time Up and Go Test (TUG Test): The Time Up and Go Test is an easily administered, cost-effective, and functionally relevant test to assess functional balance, mobility, strength, and fall risk. It was designed for older adults initially but was also used for the VI population to check their functional motor ability and balance [73]. It counts the time required for a participant to rise from a chair and sit down. Satisfactory test-retest reliability has been shown with an intra-cluster correlation coefficient (ICC) ranging from 0.8 to 0.85. Excellent concurrent validity has been demonstrated by a good correlation with the Berg Balance Scale [74].

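### GSR is named as skin resistance but read as rising with stress, which is the direction for skin conductance; the name or the reading rule must change

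*Protocol article*

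**What the plan says.** The article defines GSR three times, each time as resistance:

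- Table 1 legend: "GSR - galvanic skin resistance".
- Outcomes, list of secondary outcomes: "galvanic skin resistance (GSR), respiratory rate (RR), and electromyography (EMG".
- Secondary Outcomes, physiological well-being: "heart rate variability (HRV), electrocardiography (ECG), galvanic skin resistance (GSR), respiratory rate (RR), and electromyography (EMG".

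On acquisition it says only: "Two sensors placed on the index and middle fingers will acquire the data for GSR". No unit is given, skin conductance is not mentioned, and no conversion is described.

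The same paragraph then fixes how a change is to be read: "As a person becomes more stressed, GSR increases [70". It also gives its own account of what stress means autonomically, where it says of HRV that "a lower value depicts stressful conditions due to a higher sympathetic tone [67".

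**The concern.** A physiological measure can support a claim of benefit only if the direction of benefit matches the quantity recorded. Here the quantity named and the direction given do not belong together.

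The direction matters because the Objectives and hypothesis section is directional. It expects the yoga programme to improve physiological well-being and to be superior to physical exercise on it. Whether a GSR difference counts for or against those hypotheses is decided by the direction sentence alone. The Strengths section also relies on agreement between questionnaires and objective assessment. A measure read with the wrong sign would appear to disagree with the others for no physiological reason.

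**Working it through.** No figure in the plan depends on this point, so there is nothing to reproduce. The check is one of direction.

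**Step 1. Stress and autonomic tone.** The article equates stress with higher sympathetic tone (the HRV sentence in the physiological well-being paragraph).

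**Step 2. Tone and skin.** Sympathetic arousal activates the sweat glands, and moister skin conducts better. Conductance therefore rises with stress. This step is general physiology and is not stated in the article.

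**Step 3. Conductance and resistance.** Resistance = 1 / conductance. When one rises, the other falls, so resistance falls with stress.

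**Step 4. Compare with the article's reading rules.**

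| Measure | Article's direction under stress | Consistent with higher sympathetic arousal? |
|---|---|---|
| HRV | falls | yes |
| Respiratory rate | rises | yes |
| EMG | rises | yes |
| GSR, if resistance (as named) | rises | no, it should fall |
| GSR, if conductance | rises | yes |

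The stated rule fits conductance. It does not fit the quantity named.

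**Step 5. Illustration with assumed values** (none are in the article). Suppose a participant becomes calmer and conductance falls from 10 to 8 microsiemens:

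- before: 1 / (10 × 10⁻⁶) = 100,000 ohm = 100 kilo-ohm
- after: 1 / (8 × 10⁻⁶) = 125,000 ohm = 125 kilo-ohm
- change in resistance: (125 − 100) / 100 = +25%

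The rule as written would read the rise in resistance as more stress. The opposite movement holds for any positive values; the 25% only illustrates it and estimates nothing about this trial.

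**Step 6. What happens to the tests.** The Results section plans ANOVA between groups and repeated measures ANOVA within groups. For a given recorded quantity, F and p are the same whatever the direction sentence says.

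The choice of quantity is a separate matter, because the reciprocal is not linear. With assumed conductances of 5 and 10 microsiemens, the mean is 7.5, which corresponds to 1 / (7.5 × 10⁻⁶) = 133.3 kilo-ohm. The mean of the two resistances is (200 + 100) / 2 = 150 kilo-ohm. Group means, and so F and p, need not correspond between the two scales. That is a reason to fix the quantity before results by arm are seen.

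**The case against.** The strongest reply is that this may be no more than a mislabelled abbreviation. The article does not say what the polygraph exports. If it exports conductance, or if galvanic skin response was meant, the direction is correct and no result is reversed. The source cited for the direction may itself concern conductance or response, and it cannot be consulted here. This stands. The documents establish an inconsistency; they do not establish which half is wrong. Even so, the text is wrong on either branch, and nothing elsewhere in it corrects the mismatch.

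A second reply is that the direction sentence is an interpretive remark and not a scoring rule. This also stands. No cut-off, responder definition, composite or harm criterion uses GSR, and the planned omnibus tests have no preset direction. A reader might infer that relaxed participants would be scored as stressed, or that a beneficial arm is bound to be reported as harmful. The documents support neither: there is no scoring, and any misreading depends on resistance being what is recorded.

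A third reply concerns importance. The Biomarkers paragraph gives the task of objectively supporting the questionnaires to the biochemical tests, and the biomarkers are listed with the primary outcomes. GSR is secondary and plays no part in the sample size. That limits the reach of the point but does not remove it, because the hypotheses name physiological well-being explicitly.

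The shortness of a journal article is not an answer. The problem is not a missing detail but two statements that conflict within one paragraph.

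**Conclusion.** The point holds as an internal contradiction: the quantity named in three places and the direction given for it have opposite signs. This rests on the reciprocal identity and on the general physiology of sweating.

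The consequence is conditional:

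- **If resistance is recorded**, as the text consistently says, a calming effect at T1 or T2 would be interpreted as more stress in any comparison read by the stated rule. GSR would then appear to contradict HRV, respiratory rate and EMG.
- **If conductance is recorded**, interpretation is correct and the name is wrong three times.

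In both cases the effect is confined to one of the five secondary physiological measures. HADS and the sample size are unaffected, and so is the test of whichever quantity is analysed. What is at stake is whether a GSR change counts as improvement under the directional hypotheses. No trial-specific size can be put on it, since the article gives no GSR values. The correction is worth making but is not critical to the trial's main conclusion.

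**What to change.** 1. Confirm from the instrument which quantity is exported and in what unit, and state both in the physiological well-being paragraph.
2. Then take one of two routes. Either keep skin resistance and state that a higher value means less arousal, or analyse and name the outcome as skin conductance and keep the rule that a higher value means more stress.
3. Use the same definition in the Table 1 legend, the Outcomes list and the physiological well-being paragraph.
4. Settle this before any GSR data are analysed by arm. The Trial status section reports data collection as ongoing, with 62 of the planned 132 participants recruited.

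The cost is a check of the recorder's output and a change of wording; no new measurements are needed. If a conversion is chosen, take the reciprocal of the individual values and not of group means. The article does not say in what form GSR data are kept, so the team should confirm that those values are available.
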